#### Subgroup/exploratory analyses

The reporting of descriptive statistics for the primary endpoint and ranking of the two treatment arms will be repeated for the following subgroups:Those deemed compliant with treatment (consumption of > 80% of provided tablets)Those deemed non-compliant with treatment (consumption of ≤ 80% of provided tablets)

These analyses will only be repeated if enough participants meet these criteria for each treatment arm (≥ 5 participants per group).

Additionally, exploratory inferential analyses have been planned. This will involve tests of two proportions for those outcomes specifying a proportion. For the other outcomes, unpaired *t*-tests and Mann Whitney *U* tests will be used dependent on the resultant outcome distribution. For all tests, a one-sided significance level of 10% will be used to determine results of potential interest.

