**Interventions:**														
IMP dispensing		X	X		X		X		X					
IMP dose recording / review of patient diary			X		X		X		X	X	X	X		X
Prednisolone dose recording	X	X	X		X		X		X	X	X	X	X	X

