### Intervention

Participants will be blinded and receive either 400mg daily hydroxychloroquine or placebo tablets taken orally in addition to standard of care therapies. The dose will be reduced to 200 mg daily for the duration of the trial for patients who weigh < 50 kg or who have an eGFR of 30–50 ml/min.

After study treatment, participants whose eGFR dropped below 60 ml/min at any point of the trial will be asked to attend an optometrist appointment to assess near visual acuity and visual fields.

Participants will be withdrawn from the investigational medicinal product (IMP) if they develop end stage renal failure, require a critical care admission, or if they are admitted to hospital with a COVID-19 infection. The patient may resume treatment once recovered if admitted due to COVID-19. The PI may also discontinue treatment in the event of an adverse event (AE) in accordance with best medical judgement and patients may ask to withdraw from the trial at any time.

Participants will be asked to return any unused IMP and/or empty packaging at each trial visit. The study drug returns will be returned to pharmacy for accountability. Participants will also be prompted to complete a weekly diary to record compliance. If compliance is ≤ 80%, the investigator should counsel the patient and ensure steps are taken to improve compliance. Any instances of a patient with > 120% compliance (considered an overdose) will be escalated to the trial management group (TMG) and the trial steering committee (TSC) in addition to the patient receiving counselling. Secondary levels of monitoring are provided by the DMC as part of interim data reviews and blood hydroxychloroquine levels.

Blood samples will be collected at four visits across the trial in order to analyse the levels of hydroxychloroquine in the blood. This analysis will be completed after the trial has ended to maintain blinding to treatment allocation. Samples will also be collected and stored for future research into AAV.

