The following exploratory outcomes will be examined:Proportion of patient with incidence of new diabetes mellitus*Proportion of patients with dyslipidaemiaMedian Functional Assessment of Chronic Illness Therapy (FACIT) [25] score at each time point and the median relative change in FACIT score from baseline to week 52/56*Median scores in quality-of-life measures: SF-36 [26], EQ5D [27], Health Assessment Questionnaire (HAQ) [28] and AAV Patient Reported Outcome (PRO) [29] at each time point and the median relative change in the same quality of life measures from baseline to week 52/56*Median Glucocorticoid Toxicity Index (GTI) [30] at each time point and the median relative change in GTI from baseline to week 52/56Median Physician’s Global Assessment (PGA) [31] at each time point and the median relative change in PGA from baseline to week 52/56*Mean ANCA titres at each time point and the median relative change in ANCA titres from baseline to each time point*Proportion of patients with medicine compliance of ≤ 80%Mean absolute values and relative change from baseline to each time point in renal variables: serum creatinine, serum albumin, urine protein to creatinine ratio*

Participants wishing to stop trial medication will be asked to continue trial visits and data collection if willing. Otherwise, they will be withdrawn from the trial.

In the case that a participant withdraws more than 4 weeks since their last hospital visit, they will be invited to attend a withdrawal visit or a telephone interview. Data contributing to the asterisked (*) outcome measures above will be collected if feasible during this visit. Data collected prior to participant withdrawal will be included in the statistical analysis where possible.

It is anticipated that the withdrawal rate for this cohort of patients will be < 5% [21, 32, 33]. No specific plans have been made to ensure participant retention as this low withdrawal rate is based on similar studies in AAV patients. However, participants will be contacted via the telephone between hospital visits which are longer than 4 weeks apart to provide regular contact and encourage participants to report AEs.

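### Compliance subgroups are defined by tablets provided, so a participant who stops early with few tablets left can be ranked as compliant

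*Protocol article*

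**What the plan says.** In the protocol article, Subgroup/exploratory analyses, the primary endpoint description and the ranking of arms are to be repeated in two groups. The compliant group is defined by "consumption of > 80% of provided tablets" and the non-compliant group by "consumption of ≤ 80% of provided tablets". The cut in both is thus "80% of provided tablets". Each is reported only if there are at least five participants per group.

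The word compliance appears in two other places, neither with a denominator:
- Under Intervention there is a lower trigger, "If compliance is ≤ 80%, the investigator should counsel the patient", and an upper one, "Any instances of a patient with > 120% compliance (considered an overdose) will be escalated". The same section names two data sources: drug returned at each visit and a weekly diary.
- Under Outcome measures, an exploratory outcome reads "Proportion of patients with medicine compliance of" 80% or less.

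The row "IMP dispensing" in Table 1 marks baseline and weeks 4, 16, 28 and 40. Trial design sets treatment at 52 weeks. Under Outcome measures, participants who want to stop the drug are asked to keep attending and providing data, and the primary outcome covers the final 12 weeks.

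**The concern.** A ratio of tablets consumed to tablets provided stops growing in its denominator once no further pack is issued. It measures how fully a person used what was handed over, not how much of the planned course was taken. A compliance subgroup is usually meant to show the result in people who took the drug. Here it can include people who took none during the endpoint window, and who have endpoint data because they stayed in follow-up.

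The same shift takes people out of the non-compliant group, which makes that group more likely to miss the minimum of five and go unreported.

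There is also a question of meaning. A threshold above 120% cannot be met by a ratio whose numerator is part of its denominator, so the word must mean something else under Intervention than it does in the subgroup definition.

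**Working it through.** The plan gives no computed figure on this point, so there is none to reproduce. The check compares two denominators.

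**Inputs.** Dispensing days 0, 28, 112, 196 and 280 and the 364-day course come from Table 1. The 80% cut comes from Subgroup/exploratory analyses. Pack size is not stated, so it is varied below.

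**Step 1: stopping exactly at a dispensing visit, exact-fit packs, all tablets taken.** Consumed/provided is 100% each time. Consumed/planned is:
- week 4: 28/364 = 7.7%
- week 16: 112/364 = 30.8%
- week 28: 196/364 = 53.8%
- week 40: 280/364 = 76.9%

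All four fall at or below 80% of the course, yet all four are classed as compliant.

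**Step 2: how wide the affected windows are.** With exact-fit packs and full intake until stopping, a stop at week t is classed as compliant when t exceeds 0.8 × the weeks supplied so far.

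| Weeks supplied | 0.8 × supplied | Stops classed as compliant | Share of course taken |
|---|---|---|---|
| 4 | 3.2 | weeks 3.2-4 | 6-8% |
| 16 | 12.8 | weeks 12.8-16 | 25-31% |
| 28 | 22.4 | weeks 22.4-28 | 43-54% |
| 40 | 32.0 | weeks 32-40 | 62-77% |

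Stops up to week 0.8 × 52 = 41.6 leave at most 80% of the course taken. The windows sum to 0.8 + 3.2 + 5.6 + 8.0 = 17.6 weeks, and 17.6/41.6 = 42%. The other 58% of such stop times are already classed as non-compliant. These are shares of calendar time, not forecasts of how many people stop then.

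**Step 3: sensitivity to pack size (assumption).** Suppose each pack holds 7 spare days, all counted as provided. Cumulative supply is then 5, 18, 31 and 44 weeks at the last moment before weeks 4, 16, 28 and 40.
- Scores for stopping at those visits: 4/5 = 80% (non-compliant), 16/18 = 89%, 28/31 = 90%, 40/44 = 91%.
- Affected windows: weeks 14.4-16, 24.8-28 and 35.2-40, summing to 1.6 + 3.2 + 4.8 = 9.6 weeks, and 9.6/41.6 = 23%.
- A participant who takes every dose for 52 weeks scores only 364/399 = 91%.

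The measure thus depends on pack size as well as on behaviour.

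**Step 4: the trigger above 120%.** Consumed tablets cannot exceed provided tablets, so that ratio is at most 100%. Against a prescribed dose the trigger can be reached: with the same 7 spare days, taking the whole first pack in its interval is 35/28 = 125% of prescribed, while still 100% of provided.

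**The case against.** The strongest reply is that the article is a condensed text and that taking drug as supplied is a legitimate construct, distinct from persisting to week 52. The first part does not answer the point, because the article states the denominator in words rather than leaving it out. The second part is fair as a definition, but it does not suit a subgroup used to re-rank the arms on an endpoint in the final 12 weeks.

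Four stronger readings are tempting, and the documents do not support them:
- **A reader might infer that every early stopper scores 100%.** That needs exact-fit packs, no returns and a stop at a dispensing visit. Many mid-pack stoppers return enough tablets to fall at or below 80%.
- **A reader might infer that the compliant group is largely untreated.** Stoppers at weeks 28 and 40 took 54% and 77% of the course, and nothing shows that such stoppers would dominate the group.
- **A reader might infer that the exploratory compliance outcome is understated.** That follows only if it uses the subgroup definition. Outcome measures gives it no denominator.
- **A reader might infer that the escalation rule above 120% is unworkable.** Intervention names no denominator either, and prescribed dose or the diary would make it workable. What stands is that the two uses are not reconciled.

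Two further objections stand in part. The stakes are modest: expected withdrawal is below 5%, which is under 4 of 76 participants, and the number who stop drug but stay in follow-up is not given, so the effect on the ranking cannot be sized. Also, a planned-course denominator puts people taken off drug on medical instruction in the group at or below 80%, and such stopping may differ between arms. That is a real cost, to be met by reporting. Hydroxychloroquine blood levels at four visits give a separate check on exposure, but only in the active arm.

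**Conclusion.** The concern holds in a limited form. The stated rule lets a participant who stops at or shortly before a dispensing visit, with few tablets left, be ranked as compliant after taking far less than 80% of the course and while off drug in the endpoint window. Assuming full intake until stopping, this covers about 42% of the stop times that leave at most 80% of the course taken if packs fit exactly, and about 23% with 7 spare days per pack.

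The effect is confined to the descriptive ranking in the compliance subgroups and, if it shares the definition, the exploratory compliance outcome. The main ranking and the sample size are untouched. The three uses of compliance need one reconciled meaning, or separately named ones.

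**What to change.** For the subgroup analysis and the exploratory compliance outcome, define compliance as tablets taken divided by tablets prescribed for that participant over the scheduled 52 weeks, with time after permanent discontinuation counted as not taken. Report by arm how many in the group at or below 80% were stopped on medical instruction, so that readers can separate this from missed doses.

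Separately, reconcile Intervention, Outcome measures and Subgroup/exploratory analyses on what compliance means and which data source feeds each use. No position is taken here on the counselling or overdose thresholds or on how they are handled.

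The cost is one definition and one extra line in a table. Dispensing, returns and diary data are already collected. The reported compliance figure will be slightly less favourable, and people taken off drug on medical instruction will fall in the lower group.

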**Research Blood Specimens:**														
Hydroxychloroquine levels		X			X		X					X		
Plasma, Serum and Cells^xiv^		X			X		X		X			X		X^xv^

^i^ Patients will be followed up by telephone at weeks 10, 22 and 34 rather than visiting the study centre. The phone call will be structured using the AAV pro questionnaire. See section 6.13 for more details

^ii^ To be arranged if a patient withdraws from the trial but is willing to have a final study visit. This is only necessary in instances where the patient’s last visit was more than 4 weeks ago

^iii^ The eye screen is only required for patients whose eGFR drops below 60ml/min at any point during the trial. The eye screen should take place between week 52 and week 56 visits by a local optometrist

^iv^ The eligibility criteria require BVAS to be scored and for female patients to have a pregnancy test at baseline as well as screening. Other screening procedures do not need to be repeated

^v^ Vital signs to include BP, pulse, respiration rate and temperature

^vi^ BVAS and VDI to be scored locally following training. BVAS scores will be quality checked by a central adjudication panel to ensure consistency

^vii^ Telephone follow up interviews will only use the AAV Pro questionnaire to structure the conversation. The SF-36, EQ5D and HAQ questionnaires will not be included

^viii^ Where ESR is not available, plasma viscosity may be used instead

^ix^ If the patient’s eGFR drops below 60ml/min at any point of the trial they should be invited for an eye screen between week 52 and 56

^x^ If the baseline visit is less than two weeks after screening, these tests do not need to be performed again

^xi^ Protein:creatinine ratio only needs to be performed if urine dipstick for protein shows 1+ or more, but results can be collected if routinely performed when the urine dipstick is negative

^xii^ Patients who test positive for hepatitis B surface antigen, hepatitis B core antibody, hepatitis C antibody or HIV-1 will be excluded

^xiii^ Urine pregnancy test

^xiv^ Plasma and serum collected at all sites. Cells at Guy’s Hospital only

^xv^ Samples only collected if the patient is identified as having a flare

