### Randomisation and blinding

Participants will be randomised 1:1 to the intervention or placebo with minimisation for ANCA (positive vs negative), age (</≥ 60 years), previous rituximab therapy (yes/no) and smoking (current smoker/non-smoker) to ensure balanced groups. Authorised staff members at each trial site will recruit participants and enter their details into a web-based randomisation system hosted by King’s Clinical Trial Unit (KCTU) to obtain treatment allocation. Blinded allocation details will be sent by email automatically to key trial site staff.

Both participants and research staff will be blinded to treatment allocation. Only the data monitoring committee (DMC) will have access to unblinded data during the trial period to safeguard patient interests. Blinded treatment supplies with unique treatment pack identifiers will be allocated through the King’s Clinical Trials Unit Intervention Management System. Evidence of unblinding of research staff completing data collection will be investigated.

Emergency code breaking services will be provided by ESMS Global with services available 24/7. Direct care teams and clinical trial personnel are permitted to receive unblinding information in the instance that the medical care of the patient is dependent on knowing the treatment allocation. Where possible, the PI will be contacted to confirm whether unblinding is necessary.

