### Outcome measures

The primary outcome is the proportion of patients at any point during the final 12 weeks of the study (± 7 days) with uncontrolled AAV disease activity (defined as BVAS > 3) OR with controlled AAV disease activity (BVAS ≤ 3) but prednisolone dose for AAV > 7.5 mg daily OR with controlled AAV disease activity (BVAS ≤ 3) but any corticosteroid use > 7.5mg daily for any reason*.

The following secondary outcomes will be examined:Median cumulative number of visits where BVAS = 0 experienced by each patient (excluding screening, baseline and week 56)Proportion of patients with deemed treatment failure at week 52Mean cumulative dosage of prednisolone*Total number of adverse events per treatment arm*Median cumulative number of infections experienced by each patientMedian number of vasculitis flares (major and minor) experienced by each patient (excluding those as screening, baseline and week 56)Median time from randomisation to remission (BVAS = 0 on two consecutive visits at least 4 weeks apart)Median time to the first severe flare with starting time points of randomisation and remission (if achieved)Median time to the first limited flare with starting time points of randomisation and remission (if achieved)Proportion of patients categorised as having a severe flare at each time point (excluding screening, baseline and week 56)Proportion of patients categorised as having a limited flare at each time point (excluding screening, baseline and week 56)Median absolute Vasculitis Damage Index (VDI) [24] at each time point and the median relative change in VDI from baseline to each time point

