### Statistical analysis

Due to the use of a selection theory (pick the winner) approach, the main analysis will not include inferential analysis. Instead, the main analysis will involve presenting the descriptive statistics for each treatment arm to demonstrate which treatment is selected (i.e. which treatment group has a lower proportion of participants meeting the primary endpoint criteria). Due to this trial design, no interim analyses have been planned.

The descriptive statistics follow those specified in the outcome measures. The primary outcome and secondary/exploratory outcomes specifying a proportion will be described as the number and proportion of participants meeting that outcome. Secondary/exploratory outcomes specifying median will be described as median and range. Secondary/exploratory outcomes specifying mean will be described as mean and standard deviation.

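### All planned comparisons are crude; a supportive estimate adjusted for entry corticosteroid dose should be prespecified beside the ranking, for a modest gain

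*Protocol article*

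**What the plan says.** All references are to the protocol article.

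- **Randomisation and blinding** names four minimisation factors: "Participants will be randomised 1:1 to the intervention or placebo with minimisation for ANCA (positive vs negative), age" (cut at 60 years), then "previous rituximab therapy (yes/no) and smoking (current smoker/non-smoker) to ensure balanced groups". Entry corticosteroid dose and BVAS are not among them.
- **Table 1** has a row for "Prednisolone dose recording" that is marked at screening and baseline. BVAS is also scored at both visits, and a footnote explains that "The eligibility criteria require BVAS to be scored" at baseline as well as at screening.
- **Outcome measures** builds the primary endpoint from those same two quantities. It begins "The primary outcome is the proportion of patients at any point during the final 12 weeks of the study" and counts BVAS above 3, or BVAS of 3 or less with corticosteroid above 7.5 mg daily.
- **Statistical analysis** makes the main analysis descriptive. The arm selected depends on "which treatment group has a lower proportion of participants meeting the primary endpoint criteria".
- **Subgroup/exploratory analyses** names the inferential methods: "This will involve tests of two proportions for those outcomes specifying a proportion", and unpaired t-tests or Mann-Whitney U tests for the other outcomes, all at a one-sided 10% level.

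No comparison is described as adjusted for, or stratified by, a minimisation factor or a baseline value. The only further breakdown of the primary endpoint is by compliance, which is observed after randomisation.

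**The concern.** Two features of the design sit badly with purely crude comparisons.

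First, balancing the arms on prognostic factors reduces the true variance of the treatment difference. A test that then ignores those factors uses a standard error that is too large and gives away part of the precision that minimisation bought.

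Second, entry corticosteroid dose is left to chance. The entry criteria shown require stable maintenance therapy but set no upper limit on the dose. A participant who enters above 7.5 mg must both reach BVAS of 3 or less and come down in dose to avoid meeting the endpoint. One who enters at or below 7.5 mg need only control BVAS without going above that dose. The endpoint's construction therefore makes entry dose plausibly prognostic, although the documents do not say how strongly.

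At stake is how a close result is read. If the arms differ visibly in entry dose and no adjusted analysis was prespecified, the imbalance can be examined only after the fact. Yet the ranking informs whether an extended study follows (Discussion).

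**Working it through.** **Inputs from the Sample size calculation section:** 36 per arm, failure 50% on placebo, true reduction 15 points (so 35% on hydroxychloroquine), stated probability of correct ranking 90%. The one-sided 10% level comes from Subgroup/exploratory analyses.

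**Step 1, the plan's own figure.** The exact two-binomial calculation gives a strict win in 88.1% of trials and a tie in 4.1%. Counting half the ties, 88.1% + 2.05% = 90.2%. By normal approximation, SE = sqrt((0.25 + 0.2275)/36) = 0.115 and Phi(0.15/0.115) = 0.904. The 90% reproduces. It is a property of the crude ranking and already averages over chance imbalance.

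**Step 2, exploratory test that ignores balanced factors.** Let R2 be the share of outcome variance that they explain. It is not in the documents, so 10-20% is assumed. The actual size of the nominal 10% test is about Phi(-1.2816/sqrt(1 - R2)):

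- R2 = 0.10: 8.8%
- R2 = 0.20: 7.6%

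The test is conservative, not inflated.

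**Step 3, what adjustment could add.** Scale the SE by sqrt(1 - R2). Power is Phi(0.15/SE - 1.2816).

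| R2 (assumed) | Correct ranking | One-sided 10% power |
|---|---|---|
| 0 | 0.904 | 51% |
| 0.10 | 0.915 | 54% |
| 0.20 | 0.927 | 57% |

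The ranking figures are upper limits. To the extent that R2 comes from minimised factors, the crude ranking already has the benefit. The formula also charges nothing for estimating coefficients.

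**Step 4, chance imbalance in entry dose.** Assume 40% enter above 7.5 mg. The SD of the between-arm difference is sqrt(2 x 0.4 x 0.6/36) = 0.115. An imbalance of at least 10 points, in either direction, occurs in about 39% of trials, and of at least 15 points in about 19%; about half of the latter, roughly 10%, is against hydroxychloroquine. Assume failure rates of 70% above and 37% at or below 7.5 mg. They average 0.4 x 70% + 0.6 x 37% = 50.2%, in line with the planned placebo rate, and imply R2 = 0.24 x 0.33^2/0.25 = 0.10. A 15-point imbalance then shifts the crude difference by 0.15 x 33 = 5 points. Against hydroxychloroquine, it lowers correct ranking from Phi(0.15/(0.115 x sqrt(0.9))) = 91.5% when balanced to Phi(0.10/(0.115 x sqrt(0.9))) = 82%.

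A simulation with one continuous covariate (6,000 trials per scenario, R2 from 0.06 to 0.39) shows the same pattern. Where the covariate was imbalanced against hydroxychloroquine by more than one SE, crude ranking was correct in 67-83% of trials and adjusted ranking in 91-94%.

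**Step 5, how many covariates.** Expected events are 36 x 0.50 + 36 x 0.35 = 30.6, about 31. In simulations on the Step 4 scenario, with only entry dose prognostic, correct ranking was:

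- crude: 90.0-90.2%
- adjusted for entry dose alone: 91.5-91.6%
- adjusted for entry dose, all four minimisation factors and baseline BVAS: 90.2-90.7%

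With no covariate prognostic, the six-covariate model lost about one point (89.1% against 90.1% crude in one run, 89.4% against 90.4% in another). Mantel-Haenszel over five binary factors would need 2^5 = 32 strata for 72 participants, about two per stratum.

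**The case against.** The strongest reply is that nothing here is invalid. A crude comparison in a randomised selection trial is unbiased, the main analysis is deliberately non-inferential, and the tests are labelled exploratory. This stands, and it is why the crude ranking should stay.

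A reader might infer that participants entering above 7.5 mg start as failures while the others do not. The documents do not support this. Everyone must enter with BVAS above 3, which alone meets the failure definition, and the endpoint is read only in the final 12 weeks. What remains is the additional dose hurdle.

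A reader might also infer that chance imbalance decides the ranking or undermines the 90%. It does not: that figure already allows for average imbalance, minimisation limits it on four factors, and the Discussion says that a win would need an extended study unless the effect is substantially larger than expected.

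The prognostic strengths are assumed, and the average gain is small. Several secondary and exploratory outcomes are also summarised as relative change from baseline, so baseline is partly used, though that is not covariate adjustment. Finally, a long covariate list could cancel the benefit. That objection is right and limits the remedy.

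What survives is narrower. The article names its tests, so the unadjusted method is stated rather than left open, and it leaves unused a baseline variable tied directly to the endpoint.

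**Conclusion.** The point holds as a modest improvement, not as an error in the design. The sample size and the 90% are correct, and the crude ranking is a valid selection rule. The exploratory tests are somewhat conservative if the minimisation factors are prognostic, at about 8.8% to 7.6% instead of 10%. Entry corticosteroid dose is recorded and plausibly prognostic, but is neither balanced by design nor used in any analysis.

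The average benefit is one to two points of correct ranking at best and about three to six points of exploratory power. Protection is larger in the minority of trials where entry dose happens to be imbalanced. All of this rests on an assumed R2 of 10-20%, and the imbalance example also on assumed entry-dose and failure rates; none of these is in the documents. A reader might conclude that every minimisation factor and baseline BVAS should be adjusted for. With about 31 events, the simulations do not support that.

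**What to change.** Keep the crude ranking as the selection rule, and add to the analysis section before unblinding:

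1. **Primary outcome, supportive estimate.** A marginal (standardised) risk difference with confidence interval from a logistic model. Covariates: entry corticosteroid dose (at or below 7.5 mg / above 7.5 mg) first, then at most one or two minimisation factors expected to be most prognostic, named in advance.
2. **Exploratory test of the primary outcome.** Base it on this adjusted estimate instead of the two-proportion test.
3. **Continuous outcomes with a baseline measurement** (for example VDI, FACIT, SF-36, PGA and renal variables). Use ANCOVA on the baseline value for the exploratory test, in a rank-based form where the outcome is summarised by a median.
4. **Disagreement.** State that the crude ranking decides, and that a different ordering on the adjusted estimate will be reported with it.

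The data are already scheduled for collection, so the cost is analysis-plan wording. The downside is slight model dependence with about 72 participants, and a loss of up to about one point in ranking accuracy for the adjusted estimate if many non-prognostic covariates are added. The short fixed list guards against that.

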One key finding from studies administering hydroxychloroquine to treat rheumatoid arthritis/SLE is the potential glucocorticoid sparing effect. Glucocorticoids to induce disease remission remain the standard of care treatment for AAV, although treatment regimens have been modified over the years to minimise the cumulative dosage administered [41]. However, glucocorticoids are associated with a wide range of physical, mental and social adverse effects including the induction of long-term complications such as hypertension, diabetes, osteoporosis, cataracts and cardiovascular events [42, 43]. Similarly, the risk of infections is high, with evidence suggesting that the continued high mortality in patients may be due to treatment-related adverse events rather than AAV itself [44].

A review of off-label use of hydroxychloroquine in patients with AAV found that patients had fewer relapses, improved symptoms and a reduced need for glucocorticoids [13], and it is anticipated that these benefits will be seen in the HAVEN trial. However, a recent study by Lane et al. has shown that hydroxychloroquine increases the cardiovascular risk to rheumatoid arthritis patients after 30 days of continuous use, and this is worsened with concomitant use of azithromycin [45]. The HAVEN protocol was amended to exclude patients taking macrolide antibiotics for long-term conditions and to reintroduce an ECG at week 16 to monitor cardiovascular safety. Previous research conducted on COVID-19 patients [46] had led to this ECG being removed.

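### The one-sided 10% rule for all exploratory tests states no direction and makes no exception for harms, and the adverse event and infection summaries can hide an excess

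*Protocol article*

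**What the plan says.** Under Statistical analysis, the protocol article says that "the main analysis will not include inferential analysis". Results are described by arm. Under Subgroup/exploratory analyses it then adds: "Additionally, exploratory inferential analyses have been planned". Two sentences assign the tests: "This will involve tests of two proportions for those outcomes specifying a proportion", and "For the other outcomes, unpaired *t*-tests and Mann Whitney *U* tests will be used dependent on the resultant outcome distribution". The level follows: "For all tests, a one-sided significance level of 10% will be used to determine results of potential interest". No alternative hypothesis is named, and no outcome is excepted.

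Under Outcome measures, the harm-type outcomes take three forms:

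- Adverse events are a count for the whole arm: "Total number of adverse events per treatment arm".
- Infections, VDI and GTI are medians. For these, "Secondary/exploratory outcomes specifying median will be described as median and range".
- New diabetes and dyslipidaemia are proportions of patients, reported as number and proportion by arm.

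Two places bear on the intended direction. The Sample size calculation is framed as ranking hydroxychloroquine superior to placebo. The Discussion paragraph of the Abstract describes the drug as safer, with fewer adverse effects than conventional immunosuppression.

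**The concern.** A one-sided test rejects in one direction only. For an efficacy outcome in a screening trial that is a reasonable choice. For a harm outcome it matters which side is tested, and the article does not say.

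- If the side is benefit, an excess of infections or diabetes on hydroxychloroquine cannot be marked as a result of potential interest, while a deficit can.
- If the side is open and chosen once the data are seen, the real level is the sum of both tails, 10% + 10% = 20%, not 10%.

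The summaries add a second difficulty. A total of events per arm does not show how many patients were affected, and one participant with many events can drive it. It also supplies one number per arm, so neither a t-test nor a Mann-Whitney test can be run on it as defined. A median count stays at 0 as long as more than half of the patients have no event.

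Relative safety is part of the case for the drug, yet the Discussion itself cites a study in which "hydroxychloroquine increases the cardiovascular risk to rheumatoid arthritis patients after 30 days of continuous use". The exploratory report should therefore be able to point either way on harms.

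**Working it through.** **Inputs.** The article gives 36 per arm, 1:1 allocation, a one-sided 10% level, and a two-proportion test for proportions. It gives no harm rates, so every harm rate below is an assumption.

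**Check of the 36 per arm.** The chance of ranking hydroxychloroquine first at 50% v 35% is Φ(0.15 / √[(0.5×0.5 + 0.35×0.65)/36]) = Φ(0.15/0.1152) = Φ(1.30) = 90.4%. This reproduces the stated 90%. The article gives no corresponding figure for harms.

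**One worked case.** Suppose a harm occurs in 11/36 on placebo and 18/36 on hydroxychloroquine.

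- Pooled proportion: 29/72 = 0.403.
- Standard error: √(0.403 × 0.597 × 2/36) = 0.1156.
- z = (18/36 − 11/36)/0.1156 = 0.1944/0.1156 = 1.68.

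A harm-side 10% test needs z ≥ 1.28 and flags this result. A benefit-side test needs z ≤ −1.28 and does not.

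**Chance of a flag when the drug truly raises the rate.** Each row sums the exact binomial probabilities of all pairs of counts that pass the pooled z-test at 36 per arm.

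| Assumed rate, placebo v drug | Benefit-side 10% | Harm-side 10% tail |
|---|---|---|
| 30% v 50% | 0.1% | 67% |
| 30% v 45% | 0.4% | 50% |
| 20% v 40% | 0.09% | 73% |
| 10% v 30% | 0.03% | 82% |
| 10% v 20% | 0.7% | 46% |
| 5% v 20% | 0.07% | 77% |

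The few benefit-side flags point the wrong way: they mark fewer harms on a drug that causes more.

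**Median infection count.** For a Poisson count with mean m, P(0) = e^(−m), so the median is 0 when m < ln 2 = 0.69. Assume means of 0.3 v 0.6:

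- P(0) is 0.74 and 0.55, so both true medians are 0 although the rate has doubled.
- The proportions with at least one infection are 26% and 45%, a visible difference.
- In simulated trials with 36 per arm, the two sample medians were equal about 66% of the time. With means of 0.2 v 0.4 it was about 98%.

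The range reported beside the median shows only the smallest and largest counts.

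**Fit between outcome and test.** The test sentences send every outcome that is not a proportion to a t-test or Mann-Whitney test. Both need a value per patient. The adverse event outcome, as defined, has none.

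**The case against.** The strongest reply is that the direction is not written, so benefit cannot be taken as settled. A one-sided test could equally look for an excess on the drug. The 67% and 50% above would then be the planned test's own power, and that test would be more sensitive to harm than a two-sided 10% test (57% at 30% v 50%). This stands. It makes the benefit-side figures conditional, but it leaves the gap in the rule: either the side is benefit, or it is open.

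Second, the infection test does not depend on the medians differing. Mann-Whitney and t-tests use the per-patient counts. With Poisson means of 0.3 v 0.6, a harm-side 10% test flags the excess in about 71% (Mann-Whitney) and 73–74% (t-test) of simulated trials. This also stands. The median is a fault of the summary, not of the test.

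Third, a reader might infer that the trial cannot flag harm at all. The documents do not support that:

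- The tests are exploratory, and the main results are described by arm, where an excess can show.
- Under Safety and Trial oversight, the data monitoring committee receives all adverse event data and sees unblinded comparative data every 6 months.
- New diabetes and dyslipidaemia are numbers and proportions of patients by arm, so the criticism of totals and medians does not reach them.
- The cited cardiovascular finding was answered with an exclusion and an added ECG. No listed outcome is cardiovascular, so changing the sidedness would not address that risk.

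Committee review protects participants during the trial, but it does not repair a rule for final reporting.

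Fourth, fixed 52-week treatment, 1:1 allocation and withdrawal expected below 5% should keep exposure similar, so ignoring exposure is a small matter here. Detailed adverse event tables may well sit in a full protocol or SAP. The sidedness rule and the form of these outcomes, however, are stated in the article and can be judged as stated.

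**Conclusion.** The point holds in a limited form. The article applies one-sided 10% testing throughout, without a direction and without an exception for infections, new diabetes, dyslipidaemia, VDI or GTI. Read as benefit-sided, which is the only direction the article's framing suggests, the tests flag a true excess of harm in under 1% of trials in every scenario tried. A harm-side 10% tail does so in about 46% to 82%. These figures rest on assumed rates, 36 per arm and a two-proportion test, so they describe proportion outcomes directly and the others by analogy.

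In addition, the adverse event total counts events and does not fit the planned tests, and the infection median can miss a doubled rate when events are infrequent.

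The defect lies in the exploratory test rule and these two summaries, not in harm detection as a whole. It does not touch the primary ranking.

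**What to change.** For harm outcomes (infections, new diabetes, dyslipidaemia, VDI, GTI, and adverse events once they have a per-patient form), replace the one-sided rule with two-sided tests or, more usefully in a descriptive trial, two-sided confidence intervals for the difference between arms. State the direction of any one-sided test that remains.

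State the two-sided level too, because it sets the sensitivity. At 30% v 50%, the harm-side chance of a flag is 67% with 10% in each tail, 57% at two-sided 10% and 41% at two-sided 5%. Keeping 10% in each tail doubles the chance of a false flag on each such outcome to about 20%, which should be said beside the results.

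Keep the adverse event total and the infection median, and add for each arm the number and proportion of participants with at least one adverse event and with at least one infection, plus event rates per patient-year.

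The cost is some wording and a little more analysis, with no new data: Table 1 already schedules adverse event reporting from baseline onward. The one downside is that unfavourable flags become possible. The change should be written down before treatment allocation is revealed to the analysts.
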